**Methods:**

This prospective multicenter (n = 10) interventional study will include 312 adult patients admitted to emergency care units with a diagnosis of moderate or severe TBI. Following inclusion and exclusion criteria, patients will be randomized, using block randomization, to receive double-blind treatment with placebo or biperiden for 10 days. Follow-up will occur at specific time windows up to 2 years. Main outcomes are incidence of PTE after TBI and occurrence of severe adverse events. Other outcomes include exploratory investigation of factors that might have benefits for the treatment or might influence its results, such as genetic background, clinical progression, electroencephalographic abnormalities, health-related quality of life and neuropsychological status. Analyses will be conducted following the safety, intention-to-treat and efficacy concepts.

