### Participants

The study will enroll adults (18 to 75 years) of both sex who fulfill the following inclusion criteria: meet the moderate or severe TBI criteria according with the Glasgow Coma Scale (GCS) [15], in such a way that GCS is between 6 and 12 at the accident scene and/or between 3 (if sedated) and 12 at hospital admission; have computerized tomography (CT) scan with evidence of acute intraparenchymal hemorrhage and/or contusion; able to receive the first dose of treatment or placebo within 12 hours of brain injury, regardless of the accident cause. Participants, or their relatives in the event of patient´s unconsciousness, will have to provide written informed consent within 48 hours from the beginning of the protocol. Exclusion criteria are: current use of biperiden or antiseizure drugs; history of epilepsy, presence of other conditions that could increase risk factors for epilepsy development, such as perinatal injuries, meningitis, encephalitis, neoplasia, acute stroke, neurodegenerative diseases; any condition precluding the use of biperiden such as pregnancy, glaucoma, benign prostatic hyperplasia, atrioventricular block or cardiac arrhythmias; megacolon or mechanical obstruction of the gastrointestinal tract and inability to perform follow-up visits (e.g. homeless patients); refusal to participate in the study and current enrollment in other clinical trial. Alcohol intoxication or other psychotropic drug use at hospital admission will not lead to protocol exclusion.

We intend to recruit participants with acute TBI from at least ten hospitals located at different regions from Brazil (North, South, Southeast, Midwest and Northeast). After a first screening at the emergency care unit (ECU) for confirming eligibility criteria (which requires standard CT scan for acute TBI cases, electrocardiogram and pregnancy test for safety), those who fulfill all criteria will be included in the study. Because the emergency scenario and the injury severity, when the participant is not able to inform his medical history and is not accompanied by an appropriate informant, consent to participate and exclusion criteria might be confirmed within two days of protocol beginning. Participants will be prospectively monitored at their respective neurology/neurosurgery centers.

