**Other Outcomes**		
Mortality incidence	Number of participants that evolved to death (all cause mortality)	24
Non-serious adverse events occurrence	Number of participants experiencing at least one non-serious adverse event	1, 3, 6, 9, 12, 18, 24
**Subgroup analysis**	Age, gender, region of lesion, occurrence of SAS, frequency and type of epileptic seizures, presence of APOEε4, educational level.	

The data analysis is based on comparisons between biperiden x placebo groups considering the end of follow up or run-in periods. PTE post-traumatic epilepsy; EEG electroencephalography; mRS modified Rankin scale. SAS symptomatic acute seizures; APOEε4 polymorphic ε4 allele of the apolipoprotein E gene.

As primary outcome, we will investigate the number of participants with unprovoked seizures, counted starting 7 days after TBI until the two years follow-up period. The presence of seizures will be clinically confirmed by a neurologist to indicate PTE. Also, as a primary outcome, the number of patients experiencing at least one serious adverse event in the two years follow-up period will be compared between placebo and biperiden groups. The ICH Guideline for Clinical Safety Data Management: Definitions and Standards for Expedited Reporting defines serious adverse event as: “A serious adverse event (experience) or reaction is any untoward medical occurrence that at any dose: results in death, is life-threatening (NOTE: The term "life-threatening" in the definition of "serious" refers to an event in which the patient was at risk of death at the time of the event; it does not refer to an event which hypothetically might have caused death if it were more severe); requires inpatient hospitalization or prolongation of existing hospitalization, results in persistent or significant disability/incapacity, or is a congenital anomaly/birth defect” [19].

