### Statistical analysis

The statistic plan followed the Guidelines for the Content of Statistical Analysis Plan in Clinical Trials [20].

Sample size calculation was performed based on previous studies [1, 2, 5–8, 10, 21] using the Pocock formula [22]. Assuming a difference in reduction of PTE of 15% between the placebo and biperiden groups at 24 months, type 1 error (alpha) of 0,05 and type 2 error (beta) of 0.10 and 20% dropout rate, 156 patients per group would be required to provide 90% power with 5% level of significance. According to epidemiological data provided by a pilot study [10], we estimated that the inclusion pace could be 3–5 patients/center/month leading to study completion within 42 months.

The hypothesis used in the analysis is that biperiden is superior to placebo. All patients who receive at least one dose of randomized study drug will be included into the safety analysis and all patients who receive at least one dose of a randomized study drug and who has an evaluable follow-up data will be included in intention-to-treat analysis. Missing data will be handled by chained-equation multiple imputation methods considering relevant baseline and outcome variables. A complete case analysis will be presented as a sensitivity analysis.

We plan to analyze the primary outcome using logistic regression, adjusting for age and sex at baseline. The result of this regression will be an odds ratio representing the relative effect of the intervention compared to the placebo. Secondary outcomes will be analyzed using appropriate generalized linear models, including logistic and linear models. Planned subgroups include type of epileptic seizures and the presence of the polymorphic ε4 allele of the apolipoprotein E gene (Table 1).

An interim analysis will be performed at 50% recruitment considering the primary outcomes. At the interim enrollment point, the DMC will consider as criteria for early interruption of the study p<0.001 for safety and p<0.0001 for efficacy analysis. The Pocock [22] stopping boundaries, will be used as a reference rather than as a rigid rule. In addition, the DMC will also consider the effect on other secondary outcomes, in the occurrence of unpredicted adverse events and external new evidence available during trial conduction.

A confidence level of 95% will be assumed for all analyses that will be conducted using Stata v17.

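### The efficacy look at 50% recruitment comes before any participant can complete the 24-month primary outcome, and its p<0.0001 criterion is practically unreachable on the few early seizures available

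*Protocol article*

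**What the plan says.** All of this is in the protocol article.

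- **Trigger (Statistical analysis).** "An interim analysis will be performed at 50% recruitment considering the primary outcomes".
- **Criteria (same section).** "the DMC will consider as criteria for early interruption of the study p<0.001 for safety and p<0.0001 for efficacy analysis". The Pocock boundaries "will be used as a reference rather than as a rigid rule", and the committee may also weigh secondary outcomes, unexpected adverse events and outside evidence.
- **Outcome (Table 1 and the text below it).** Both primary outcomes carry a 24-month timepoint. The efficacy outcome is the "number of participants with unprovoked seizures, counted starting 7 days after TBI until the two years follow-up period". The safety outcome is at least one serious adverse event over the same two years.
- **Accrual (Statistical analysis).** "we estimated that the inclusion pace could be 3–5 patients/center/month leading to study completion within 42 months". The Participants section plans at least ten hospitals, and the abstract gives 312 patients.
- **Design effect (Statistical analysis).** A 15-point difference at 24 months. The rate in each arm is not given.

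**The concern.** The look is set off by enrolment, but the efficacy outcome takes two years to mature. If recruitment runs at anything like the planned pace, the comparison is made before anyone has been followed for 24 months. A participant without a seizure at that time is not a non-case, only someone not yet observed for long enough.

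There are then two possibilities. If the committee holds to p<0.0001, the efficacy test is idle. If it uses the discretion that the section grants, an efficacy decision would rest on seizures in the first months, counted from day 7 and so starting inside the 10-day dosing period. That is a different question from whether epilepsy is prevented over two years, which is what the trial was sized to answer.

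**Working it through.** **Inputs from the article:** 312 patients, 1:1, so 156 (78 per arm) at 50% recruitment; ten centres; 3–5 patients per centre per month; completion within 42 months; outcome at 24 months; efficacy criterion p<0.0001.

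**Assumptions not in the article:** 24-month rates of 25% vs 10%; even accrual with all centres open from the start; no dropout; two-sided test; hazard either constant or front-loaded.

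**1. Reproducing the planned size.** Pocock formula: n = [p1(1−p1) + p2(1−p2)] × (1.960 + 1.282)² / (p1−p2)².
With 25% vs 10%: (0.1875 + 0.0900) × 10.507 / 0.0225 = 129.6, so 130. Then 130 × 1.20 = 156, as stated. The rates are plausible but not unique: 24% vs 9% with division by 0.8 gives 124 / 0.8 = 155.

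**2. When the 156th patient enters.**
- 5 per centre per month: 156 / 50 = 3.1 months.
- 3 per centre per month: 156 / 30 = 5.2 months.
- If the 42 months include follow-up, the last entry is by 42 − 24 = 18 months. Half is then at month 9 with even accrual, and before month 18 whatever the accrual shape.
- If all 42 months were even accrual: month 21.

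Each is also the longest follow-up of any participant at the look, and each is below 24 months. With even accrual, someone reaches 24 months by then only if accrual is at or below 156 / 24 = 6.5 per month, or 0.65 per centre per month, against 3–5 planned.

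**3. Seizures expected at the look.** Cumulative risk F(t) = 1 − (1−p)^((t/24)^k), with k = 1 (constant hazard) or k = 0.5 (front-loaded). Expected cases per arm = 78 × the average of F(u) for u from 0 to T.
Example, T = 5.2 and k = 1:
- Placebo: a = −ln(0.75) × 5.2/24 = 0.0623; average F = 1 − (1 − e^−a)/a = 0.0305; × 78 = 2.4.
- Biperiden: the same steps with 0.90 give 0.9.
- Total: 3.3.

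**4. What p<0.0001 requires.** With 78 per arm and the pooled two-proportion z test (critical value 3.891):
- 14 vs 0: z = 0.1795 / 0.0458 = 3.92, which crosses.
- 13 vs 0: z = 3.77, which does not.
- With one case on biperiden, 17 vs 1 is needed.

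Fisher's exact test gives the same two minimum splits.

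**5. Chance of crossing under the design effect.**

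| Month of look | Expected cases, both arms (k = 1 to k = 0.5) | Chance of p<0.0001, at most |
|---|---|---|
| 3.1 | 2.0 to 7.1 | 0.01% |
| 5.2 | 3.3 to 9.1 | 0.05% |
| 9 | 5.6 to 11.9 | 0.2% |
| 21 | 12.5 to 17.6 | 1.2% |

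Even with all 156 followed for 24 months: expected z = 0.15 / √(0.2775/78) = 2.51, and P(Z > 3.89 − 2.51) is about 8% (about 7% with pooled variance under the null).

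**6. Other rates.** The Introduction gives 17–27% for severe injury. I repeated step 5 for 17% vs 2%, 20% vs 5% and 27% vs 12%, summing the binomial probabilities. The chance stays at or below about 0.2% up to month 9 and 1.7% at month 21. With full follow-up it runs from 5% (27% vs 12%) to 17% (17% vs 2%).

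**7. The safety half.** At 30–50 entries per month, about 10–17 of the 156 entered in the last 10 days. About 139–146 are therefore past the 10-day treatment period at the look.

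**The case against.** The strongest reply is that the efficacy outcome is cumulative. A seizure confirmed before the look already makes that participant a case at 24 months, seizures at 1, 3, 6 and 9 months are a listed secondary outcome, and nothing says that the look requires completed follow-up. This stands against one tempting reading, that the look has no efficacy data at all. It has some, but too few to reach the criterion, and none that classify the seizure-free.

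A reader might also infer that the whole interim is empty, or that it could spare nobody. The article does not support either. Serious adverse events around treatment will be available for most of the 156, the p<0.001 criterion can be applied to them, and a stop at 156 of 312 could spare up to 156 later patients.

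Nor is a low crossing chance a fault in itself, since a strict threshold is meant to be hard to cross. The low chance also means that a mistaken stop under the stated criterion is very unlikely, and no harm to the final analysis has been shown. The fault is that the trigger and the outcome do not fit, and that the discretion granted leaves room for a decision on early seizures alone.

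Finally, the data cut for an interim is often left to the analysis plan or the committee's charter. That would excuse silence on follow-up time. Here, however, the article itself fixes the trigger, the outcomes, their timepoint and the thresholds, and these do not fit together.

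**Conclusion.** The efficacy part of the interim is wrong as written. The timing result needs only the article's own figures and steady accrual: 0 of 156 participants will have completed 24 months. If the 42 months include follow-up, it holds for any accrual shape. If they are all accrual, it needs a roughly even pace. Staggered opening of centres would lengthen the earliest follow-up, but under steady accrual the total would have to fall to 6.5 per month to change the result.

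That the criterion is practically unreachable rests on assumed arm rates and hazard shapes. It held over every combination tried: at most about 0.2% up to month 9 and between 1% and 2% at month 21. The conclusion is limited to the efficacy test. It does not extend to the safety look, and it does not say that the trial's type 1 error is inflated.

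**What to change.** Keep the look at 50% recruitment as a safety review of serious adverse events and deaths to date, with the safety criterion already stated, and delete the efficacy test there. If an efficacy look is wanted, trigger it on completed 24-month follow-up or on a stated number of confirmed cases of post-traumatic epilepsy, and say which.

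The cost is a few sentences in the protocol and the monitoring committee's charter, with no added patients or visits. It should be settled before the committee sees unblinded data.

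The downside is that no formal efficacy stop remains during enrolment. Waiting for the first 156 to reach 24 months puts the look at 3.1 + 24 = 27 to 5.2 + 24 = 29 months, or 9 + 24 = 33 months with 18 months of accrual. Recruitment would have ended by month 6.2–10.4 (312/50 to 312/30) or month 18. The loss is small, because the present look has almost no chance of crossing.

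### The interim rule gives p<0.0001 for efficacy and then names Pocock boundaries as the reference; the two do not match, and only the first fits a final test at 5%

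*Protocol article*

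**What the plan says.** All the relevant text is in the Statistical analysis section of the protocol article.

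- Timing of the look: "An interim analysis will be performed at 50% recruitment considering the primary outcomes".
- Criteria given to the DMC: "criteria for early interruption of the study p<0.001 for safety and p<0.0001 for efficacy analysis".
- The sentence that follows: "The Pocock [22] stopping boundaries, will be used as a reference rather than as a rigid rule".
- Final level: "A confidence level of 95% will be assumed for all analyses that will be conducted using Stata v17". The sample size uses the same level: "156 patients per group would be required to provide 90% power with 5% level of significance".

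The article does not say how the two interim criteria relate to the Pocock boundaries. It gives no nominal Pocock level, no adjusted level for the final analysis and no sidedness.

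**The concern.** The explicit criteria are fixed, very strict interim thresholds of the Haybittle-Peto type. They spend almost no alpha, so the final test can stay at 5%. A Pocock boundary works the other way: it applies one moderate level at every look, and the final test must use that reduced level too. The section names both and keeps the final level that suits only the first.

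Two things are at stake. First, an interim efficacy result of, say, p=0.005 fails the explicit criterion but crosses the Pocock boundary, so the DMC's guidance points in two directions. Second, whether the trial holds its 5% error depends on which sentence the DMC follows.

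**Working it through.** **Inputs from the article (Statistical analysis).** One interim and one final analysis; interim efficacy p<0.0001; overall alpha 0.05; final analysis at 95% confidence; 156 per group; 20% dropout; 90% power; a 15% difference at 24 months.

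**Assumptions (not in the article).** Two-sided testing. Half of the statistical information at the interim (t = 0.5), with lower values as a range, because the look is tied to 50% recruitment while the outcome runs to 24 months. For power only: 25% vs 10%, reading 15% as absolute points. The control rate is not stated; the Introduction gives 2.9% for moderate and 17–27% for severe TBI.

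**1. The plan's own sample size.** Unpooled formula: n = [p1(1−p1) + p2(1−p2)] × (1.960 + 1.282)² / d² = (0.1875 + 0.09) × 10.51 / 0.0225 = 129.6, so 130 per group. Then 130 × 1.2 = 156. A single-look, two-sided 5% design with no allowance for a Pocock boundary therefore reproduces the stated 156 under the assumed rates. This supports that reading but does not prove it. For example, 24% vs 9% gives 124 per group, and 124/0.8 = 155.

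**2. The Pocock level.** Overall error = 1 − P(|Z1| < c1, |Z2| < c2), with (Z1, Z2) bivariate normal and correlation √t. Setting c1 = c2, t = 0.5 and overall error 0.05 gives a nominal level of 0.02939 (|z| = 2.18). The stated criterion p<0.0001 is |z| = 3.89. The ratio is 0.0294/0.0001 = 294.

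**3. Overall two-sided error for each combination.**

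| Interim level / final level | t = 0.5 | t = 0.3 | t = 0.2 | t = 0.1 |
|---|---|---|---|---|
| 0.0001 / 0.05 | 0.0500 | 0.0500 | 0.0501 | 0.0501 |
| 0.0294 / 0.05 | 0.0674 | 0.0720 | 0.0741 | 0.0760 |
| 0.0294 / 0.0294 | 0.0500 | 0.0536 | 0.0551 | 0.0566 |

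With p<0.0001 at the interim and t = 0.5, the final level that keeps exactly 0.05 is 0.04999, so no practical adjustment is needed. If testing were one-sided at 0.05, the Pocock level would be 0.0304 and the second row at t = 0.5 would be 0.066; the conclusion is the same.

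The third row shows that 0.0294 is itself correct only at half information. At t = 0.1 to 0.3 the equal level that holds 5% is about 0.026 to 0.027.

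**4. Power if a Pocock design were really meant (25% vs 10%, t = 0.5).** With 125 per arm (156 × 0.8 = 124.8), the expected final z is 0.15/√(0.2775/125) = 3.18. With 130 per arm it is 3.25.

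| Analysed per arm | Single test at 0.05 | Two-look Pocock, 0.0294 at both |
|---|---|---|
| 125 | 88.9% | about 86% |
| 130 | 90.1% | about 87% |

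The loss is about 3 percentage points. Restoring 90% takes about 10% more patients.

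**The case against.** The strongest reply is that the article gives only one numerical efficacy threshold, p<0.0001, and that the plan is coherent under it. The figure 0.0294 is nowhere in the text. The Pocock sentence is expressly advisory ("stopping boundaries, will be used as a reference rather than as a rigid rule"), and the same reference [22] is cited for the sample-size formula, so it may be meant only as background for the criteria just stated. Non-rigid guidance to a DMC is normal, and detail may sit in a charter that is not shown.

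Much of this stands. A reader might infer that the trial's type I error is already above 5%. The documents do not support that: the excess arises only if the DMC stops for efficacy at a looser boundary than its stated criterion. A reader might also infer that the final test must move to 0.0294, with power of about 84%. That does not follow either. At 125 per arm, 84% is the power of the final look alone and leaves out rejections at the interim. Moreover, 0.0294 at both looks exceeds 5% when less than half of the information is in.

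What does not stand is that advisory status removes the conflict. Judgement around one boundary is ordinary. Here the named reference boundary is a different kind of rule from the criteria beside it and implies a different final level. This is not detail left to a charter: the article states both rules, and a charter drafted from it would inherit both.

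**Conclusion.** The point holds as a conflict between two stated interim boundaries. Under the explicit criterion, overall two-sided error is 5.00% and the 5% final test is valid. If the DMC acts on the Pocock level for efficacy and the final test stays at 5%, the error is 6.7% at half information and 7.2% to 7.6% at 30% to 10% information. These figures assume two-sided testing and the classical equal-level Pocock boundary. The power figures rest in addition on the assumed 25% vs 10%. The correction should be made before the DMC sees unblinded data.

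**What to change.** Delete the Pocock reference from the interim paragraph, or state that it does not govern stopping for efficacy. State that two-sided p<0.0001 is the efficacy boundary at the interim and that the final analysis is tested at 0.05. Use the same wording in the DMC charter, and say there whether the Pocock sentence was meant to bear on the safety criterion. This is a one-sentence edit with no loss of power and no change in sample size.

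If a Pocock-type design is really intended, compute the level for the information actually available at the interim, use it at both looks with matching confidence intervals, and restate power from the two-look design. That power is about 86–87% at 125–130 analysed per arm under the assumptions above. Keeping 90% would cost about 10% more patients.

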## Discussion

This is a multicentric interventional prospective study aiming to evaluate the efficacy and safety of biperiden in preventing the development of epilepsy in patients that suffered TBI, in a double blind, randomized, placebo-controlled trial. If successful, it will be the first antiepileptic drug and will confirm the safety of the drug in patients with TBI, with the advantage of having low cost and good availability given it is a medication already in use in the clinical practice and which has been extensively used for another medical condition.

The process of epileptogenesis has been the subject of numerous studies and despite some promising results in laboratory settings no compound has yet advanced to the clinical practice [23]. Both clinical and laboratory evidence suggest crucial roles for the glutamatergic and the GABAergic systems in the expression and suppression of seizures and also in the development of the epileptic condition. The cholinergic system on the other hand, raises a limited interest from the clinical perspective (with some notable exceptions such as soman and sarin) in the epilepsy arena [24]. However, recently different strategies to modulate neuronal cholinergic activity have been shown to be effective at modifying the epileptogenic process in preclinical studies [10, 12]. Among various approaches, acute treatment with biperiden, showed to hamper the development of PTE in animal models of brain injury [11].

Here we move forward by developing a clinical trial, in which biperiden will be administered in brain injured patients as soon as possible after the traumatic brain injury and only for a period of 10 days. The emergency room settings as well as the critical patient conditions (often life threatening) in addition to the long-term period (2 years) to follow up patients, imposes practical and operational hurdles for the successful development of the study. A pilot study carried out under similar conditions [10] helped to outline the main difficulties and strategies to overcome these limitations, as discussed below.

Because treatment has to be administered soon after injury, and because severe trauma patients may be unconscious and not accompanied by a legal responsible person at the hospital admission, research ethics committees from all study centers allowed an extended deadline of 48h to obtain the informed consent to the study after beginning treatment, in order to guarantee effective enrollment rate. Also, because some aspects of the clinic history may not be readily available during enrollment, some inclusion and exclusion criteria will be checked over the initial course of treatment, which may result in high exclusion rate of patients. In that case, data from those patients will be considered only for safety analysis.

The dose of intravenous injection of biperiden is similar to the maximum recommended dose to initiate treatment of severe cases of parkinsonism [25] and also showed to be safe in critical TBI patients [10]. However, severely injured patients receive a variety of treatments and drug interventions and, in addition to the evolution of the clinical condition, all those are confounding factors that must be taken in account when registering adverse effects that might be caused by the biperiden treatment. We will focus the analysis of adverse effects on the symptoms already described for biperiden without underestimating additional unreported occurrences, mainly during treatment, and its correlation with other possible causes.

The long-term assessments in different areas (EEG, neuropsychology, etc) will be conduct by specialized staff (neurologists, neurophysiologists, trained psychologists). To decrease loss of data associated to absence of the patient in presential visits on specified time points, e.g because social restrictions due COVID-19 pandemic or other reasons, essential data related to clinical evaluation of seizures development will be collected by phone calls, as necessary. Different contact options, such as relatives phone numbers and e-mail addresses will be collected and only after many frustrated attempts of contact for different clinical assessments, patients will be considered lost in the follow up.

The present study will focus on patients with moderate to severe TBI, comprising the group with the highest risk to develop PTE. While the pathogenesis of epilepsy development after brain injury remains unclear, the search for earlier biomarkers and for new resources that might enable to identify patients who could benefit from prophylactic treatments are additional highlights of this work. We also will investigate whether the anticholinergic actions of biperiden may also have some impact on other outcomes or sequelae after TBI. Accordingly, the present study will provide major information related to: (i) the proportion of patients who develop PTE in addition to those who die in the two-year follow up period after TBI; (ii) other aspects of the patients`neurological outcomes that may benefit from early treatment, such as degree of disability or dependence in the daily activities, general life quality and neuropsychological dimensions; and (iii) the incidence of different ApoE polymorphisms, more importantly of APOEε4 and its putative association to epileptogenesis and treatment effectiveness.

An additional positive aspect of this project is to use an already known drug, affordable and widely used to treat another neurological pathology, being part of the list of Essential Medicines developed by the World Health Organization which indicates medicines to be always available within general health systems in adequate amounts. In the event this drug is shown to be effective in reducing epilepsy after TBI in humans it would be readily available for use as an off-label indication. Moreover, it might also have the potential to be used to mitigate the development of epilepsy secondary to other pathologies, such as after stroke.

